### Recruitment {15}

All patients admitted to a tertiary hospital in Victoria, Australia (The Austin Hospital), may be screened for potential recruitment. A daily 24-h report of all admitted patients with hyponatraemia will be extracted from the hospital electronic database (Cerner Millennium) at 0800 hours each morning. Based on this extract, the written and electronic medical records of potential participants will be screened for eligibility by study personnel. Eligible participants will be approached in person on the ward.

All of the information required for ensuring participant eligibility is obtained as part of clinical routine care of the hyponatraemic patient. However, if by oversight the clinical team has not performed a relevant blood or urine test, those will be requested by study personnel for the purposes of assessing eligibility.

## Assignment of interventions: allocation

### Sequence generation {16a}

Randomisation will be stratified according to volume state (euvolaemic or hypervolaemic) which will be defined based on the presence or absence on clinical examination of detectable dependent pitting oedema and assessment of jugular venous pressure. Randomisation will be further stratified by serum sodium concentration (Na < 123 mmol/L or Na ≥ 123 mmol/L) to ensure even distribution of biochemical severity between groups.

Four randomisation sequences based on computer-generated random numbers with varying block size (2–6) will be generated and concealed from study personnel for the duration of the study.

### Concealment mechanisms {16b}

The allocation sequence for each stratification subgroup will be placed in sequentially numbered sealed envelopes by Austin Health Clinical Trials Pharmacy staff.

### Implementation {16c}

The allocation sequences will be generated by Austin Health Clinical Trials Pharmacy staff, independent of study personnel and sequential concealment envelopes prepared. Study personnel will recruit potentially eligible patients on the ward. When a participant consents to be enrolled in the trial, they will be assigned a study number and the next sequential envelope will be accessed and opened to reveal their allocation, based on their stratification subgroup (hypervolaemic or euvolaemic, and sodium level below or above/at 123 mmol/L) to allocate the participant to one of two study arms (tolvaptan or fluid restriction). The intervention will then be communicated to the treating team, and if allocated to tolvaptan, tolvaptan will be prescribed by standard electronic prescribing methods and administered by clinical ward staff.

## Assignment of interventions: blinding

### Who will be blinded {17a}

This trial is open-label due to the nature of the interventions (fluid restriction, versus administration of tolvaptan tablet with free fluid intake). The participants’ randomised allocation will only be revealed to the investigator and participant after enrolment is complete.

### Procedure for unblinding if needed {17b}

There will be no unblinding procedure undertaken.

## Data collection and management

### Plan for assessment and collection of outcomes {18a}

Data will be collected with the use of Research Electronic Data Capture (REDCap) software hosted by Austin Health [29, 30]. This is a secure, web-based software platform designed to support data capture for research studies that is widely used in research. REDCap provides (1) an intuitive interface for validated data capture, (2) audit trails for tracking data manipulation and export procedures, (3) automated export procedures for seamless data downloads to common statistical packages and (4) procedures for data integration and interoperability with external sources. Where possible, repeat measures will be performed by a single researcher, who will be a doctor with experience in hyponatraemia management, or alternative healthcare personnel with appropriate training in the specifics of this trial. The following study measures have been built into the REDCap project application.

#### Demographics

Demographic information will be collected including name, date of birth, age, hospital record number and contact phone number (for patient or medical treatment decision maker). Patients will subsequently be identified by a study number. We will also collect information including place of residence (home versus supported care) and evaluation of baseline functional status in the form of the European Cooperative Oncology Group (ECOG) score [31] and whether the participant requires assistance to complete their activities of daily living. We will also collect a list of medical diagnoses and regular medications which will be relevant with respect to inclusion and exclusion criteria, and will inform calculation of a Charlson comorbidity index score [32] alongside a record of the presumed underlying cause of hyponatraemia.

#### Screening

A screening questionnaire will ensure that inclusion and exclusion criteria are met (see above). This requires results from a number of routine investigations to be available, e.g. serum sodium and potassium levels, serum glucose level, urine sodium and specific gravity, cortisol level, thyroid function tests and estimated glomerular filtration rate, plus clinical assessment of conscious state and volume status. If the patient is eligible for the trial and informed consent is obtained, they will be allocated to a treatment arm.

#### Treatment questionnaire

Once allocation has occurred according to the randomization process, a daily treatment questionnaire will monitor progress and assist in implementation of the titration protocol (Tables 1 and 2). Daily biochemistry and 24-h sodium increment will be recorded to determine the intervention for the following 24 h. Details of any potential adverse events, including requirement for intravenous dextrose to mitigate serum sodium rise, are recorded as escalated as required.

##### Biochemistry

Sodium measurements will be performed with simultaneous indirect urea, electrolytes and creatinine and direct measurement with venous blood gas will monitor serum sodium. In patients with serum sodium below 125 mmol/L and all patients following tolvaptan administration, bloods will be performed every 6–8 h in accordance with recommendations [7, 28]. Patient with serum sodium above 125 mmol/L being managed with a fluid restriction (not tolvaptan) will have bloods every 12 h. In the event of discrepancy between these readings, the direct sodium measurement will be preferred due to increased accuracy and faster turnaround time [33]. Daily serum osmolality will be recorded. A daily urine sample at 0600 will monitor urine sodium, osmolality and specific gravity. Daily monitoring of liver function will be performed in tolvaptan recipients for safety given the small risk of liver damage identified in longer-term trials of high-dose tolvaptan used for other indications [23].

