Currently, tolvaptan use in hospitalised patients with moderate to profound hyponatraemia is not evidence-based as there are no randomised controlled trials comparing the use of tolvaptan in hospitalised patients against standard of care fluid restriction. International guidelines are divided on the use of tolvaptan in hyponatraemia with lower sodium concentrations, due to concern regarding risk of sodium overcorrection [4, 7]. European guidelines recommend against the use of tolvaptan in moderate-profound hyponatraemia [7], whereas US/Irish guidelines acknowledge that there is insufficient evidence for tolvaptan use with serum sodium < 120 mmol/L, but endorse its use with appropriate monitoring of serum sodium levels, and prompt intervention if the recommended rate of serum sodium increase is exceeded [4]. Other potential concerns raised about tolvaptan include cost [22] and risk of liver function derangement seen with sustained higher-dose tolvaptan therapy for other indications (e.g. autosomal dominant polycystic kidney disease) [23].

Thus, there is a critical evidence gap with respect to efficacy and safety of tolvaptan in the very patients for whom it would be most useful. As such, there is physician reluctance to use what may be a safe and more efficacious therapy than fluid restriction if prescribed appropriately. There is an international need for rigorous randomised comparisons between tolvaptan and fluid restriction to determine evidence-based protocols for the use of tolvaptan in hospital inpatients with moderate to profound hyponatraemia, to clarify its role and ensure optimal patient outcomes.

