### Objectives {7}

Aim: To compare the efficacy and safety of tolvaptan versus a rigorous, protocol-based fluid restriction to raise serum sodium levels in acute hospital inpatients with moderate-to-profound euvolaemic or hypervolaemic hyponatraemia.

Hypothesis: Tolvaptan will be more effective than fluid restriction in raising serum sodium and will lead to faster improvement in hyponatraemia-related symptoms, reduced length of hospital stay, without increasing adverse events.

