#### Relevant concomitant care permitted or prohibited during the trial {11d}

Fluid restriction will not be allowed for participants in the tolvaptan group on days that they receive tolvaptan. Tolvaptan will not be allowed for participants in the fluid restriction arm. Otherwise, management decisions will be the responsibility of the treating team. This includes the use of other treatments for hyponatraemia including diuretics, oral solute, or intravenous saline. The treating medical team will retain the authority to withdraw a participant from the trial for any reason.

In the event that a patient becomes significantly hypovolaemic (as demonstrated by development of hypotension or serial urine sodium newly < 20 mmol/L), the patient will not receive either tolvaptan or fluid restriction and may be prescribed intravenous normal 0.9% saline at the discretion of the treating team.

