### Adverse event reporting and harms {22}

During the study, from the time the informed consent is signed by the patient until 28 calendar days following the study participation, safety information will be collected by means of completing case report forms and adverse event forms.

Adverse events will be reported to the trial Data Safety and Monitoring Board who will determine whether any protocol amendment or discontinuation is warranted.

In addition, Serious Adverse Events and Product Quality Complaints relating to tolvaptan will be reported to the sponsor University of Melbourne and the funding source Otsuka Australia Pharmaceutical within 24 h of first awareness of the event for submission to the Global Pharmacovigilance database. The collection period of safety information is from the first use of tolvaptan until 28 calendar days after discontinuation. De-identified participant data (for example, referring to patients using their sex and age or date of birth, but not their names or contact details) may be sent to Otsuka. Serious adverse events and all other safety information will be included in the Final Study Report to Otsuka at the end of the study.

As stated, the sponsor, University of Melbourne, and the funding source, Otsuka Australia Pharmaceutical, have no role in the study design, data analysis or manuscript preparation.

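### Liver function is scheduled daily for tolvaptan recipients and not for the fluid-restriction arm, so laboratory liver abnormalities lack a matched control rate (minor, cheap to fix)

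*Protocol article*

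**What the plan says.** The Biochemistry section sets the schedule: "Daily monitoring of liver function will be performed in tolvaptan recipients for safety". It gives the reason as the "small risk of liver damage identified in longer-term trials of high-dose tolvaptan used for other indications". The same paragraph makes serum osmolality and the urine tests daily with no limit to one arm, so the limit on liver tests looks deliberate.

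Controls cannot come under the liver schedule by another route, because section {11d} says "Tolvaptan will not be allowed for participants in the fluid restriction arm".

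The Background {6a} lists, among the concerns raised about the drug, "risk of liver function derangement seen with sustained higher-dose tolvaptan therapy for other indications". The Objectives {7} expect benefit with "reduced length of hospital stay, without increasing adverse events", which is a statement about the difference between arms.

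Section {22} collects safety data in everyone: "from the time the informed consent is signed by the patient until 28 calendar days following the study participation, safety information will be collected". It attaches no liver test schedule to that collection. A second window in the same section, "The collection period of safety information is from the first use of tolvaptan until 28 calendar days after discontinuation", sits with the reporting of tolvaptan events to the sponsor and funder. It adds no liver testing in controls either.

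**The concern.** A laboratory abnormality that causes no symptoms is found only if someone tests for it. Daily testing in one arm and ward-ordered testing in the other can produce different counts when the true rates are the same.

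The population makes this plausible. Participants are acute inpatients, some of them hypervolaemic, and the eligibility criteria exclude only Child-Pugh B or C cirrhosis. Liver tests may change in such patients for reasons unrelated to the allocated treatment.

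What is at stake is how a liver finding can be read. If abnormalities appear under tolvaptan, no control rate measured in the same way shows how many to expect anyway. If few appear, the trial cannot show that this matches fluid restriction. An analysis plan cannot repair this later, because it cannot recover tests that were never taken.

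**Working it through.** **No plan figure to reproduce.** The article states no liver event rate and no calculation on this point. The check is first textual, then an illustration of size.

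**Step 1: ascertainment by arm.**

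| Item | Tolvaptan | Fluid restriction |
|---|---|---|
| Liver function schedule (Biochemistry) | daily | none stated |
| Blood sampling for sodium (Biochemistry) | every 6-8 h after a dose | every 6-8 h if sodium is below 125 mmol/L, every 12 h if above |
| Adverse-event forms ({22}) | from consent to 28 days after participation | same |
| Daily record of potential adverse events (Treatment questionnaire) | yes | yes |

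Only the first row makes detection of an adverse event unequal by rule, and it concerns laboratory liver findings alone. The second row shows that control blood is already being drawn.

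**Step 2: inputs for the illustration.**
- n = 83 per arm, the recruited number in Sample size {14}. The evaluable number, 64, is used as a check.
- p = true rate of a new liver-test abnormality, the same in both arms. Assumed: 5%, 10%, 20%.
- s = share of control abnormalities that ward-ordered tests detect. Assumed: 0 to 1. Detection under tolvaptan is taken as complete.

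The article gives neither p nor s.

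**Step 3: expected detected counts.** Tolvaptan n × p; control n × p × s. With n = 83 and s = 0.5:
- p = 5%: 83 × 0.05 = 4.2 against 2.1
- p = 10%: 8.3 against 4.2
- p = 20%: 16.6 against 8.3

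**Step 4: chance of a false significant difference.** Sum Bin(i; n, p) × Bin(j; n, p·s) over all pairs (i, j) for which the two-sided Fisher test gives a p-value below 0.05. With n = 83:

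| s | p = 5% | p = 10% | p = 20% |
|---|---|---|---|
| 1 (equal testing) | 1.7% | 2.9% | 3.1% |
| 0.75 | 2.2% | 5.3% | 9.4% |
| 0.5 | 4.6% | 15.1% | 36.2% |
| 0.25 | 10.5% | 39.3% | 81.1% |
| 0 | 23.5% | 84.9% | about 100% |

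With 64 per arm and s = 0.5 the figures are 2.5%, 9.8% and 27.0%. The equal-testing row lies below 5% because the Fisher test is conservative.

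**Step 5: the extreme case.** For 6/83 against 0/83 the one-sided Fisher probability is C(83,6)/C(166,6) = 0.0142, and the two-sided value is about 0.028. This needs no detection at all in controls, so it marks the edge of the range and is not an expected result.

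**The case against.** The strongest reply is that this is ordinary monitoring of a known drug risk in the people exposed to it. Table 3 has no liver endpoint, and its named main safety outcome is sodium over-correction that prompts re-lowering treatment. Nothing in the article says that protocol-driven liver results will be pooled into a between-arm count, or that a symptomless enzyme rise will be logged as an adverse event. The bias, if any, runs against tolvaptan, so it would not by itself create a false impression of liver safety. The data monitoring board consists of independent clinicians in an open-label trial, who can know that one arm was tested by protocol. All of this stands and lowers the weight of the point. It does not supply a control rate.

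Three stronger readings are tempting, and the text does not support them.

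- **The whole adverse-event comparison is one-sided.** Section {22} collects events with no limit to one arm: "safety information will be collected by means of completing case report forms and adverse event forms". Only laboratory liver findings are unequal.
- **Control abnormalities will be missed altogether.** Biochemistry comes from routine-care samples, and wards will order some liver tests. The share detected is unknown.
- **Controls certainly have no scheduled liver tests.** The participant timeline (Table 4) is a figure that could not be read here, the article condenses a fuller protocol, and the list of screening investigations is given only as examples. What can be said is that no readable section schedules them.

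**Conclusion.** The point holds, with minor weight. By a rule stated in the article, laboratory liver abnormalities are sought daily in tolvaptan recipients and only as the ward orders in controls. A tolvaptan liver finding therefore has no matched comparison. The primary endpoint, the named main safety outcome and adverse events in general are unaffected.

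The size cannot be fixed from the document. If half of control abnormalities are detected, the false-difference risk runs from close to nominal at a 5% true rate to about one trial in three at 20%. It is much lower if wards test most controls and much higher if they test few. These figures assume equal true rates, complete detection under tolvaptan, and a formal test of liver findings between arms, which the article does not announce.

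**What to change.** In the Biochemistry section, schedule liver function for both assigned arms on the same study days: a day 1 value before allocation, then daily to day 4. Run it on the samples already drawn for urea, electrolytes and creatinine. Compare new or worsened abnormalities by arm against that day 1 value. Check Table 4 and the full protocol first, and align them with the new text.

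If control testing is not added, state that protocol-driven liver results under tolvaptan will be reported descriptively and kept out of the between-arm adverse-event comparison, including in reports to the monitoring board.

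The first option costs a laboratory add-on for at most 83 controls, four tests each (83 × 4 = 332 at most), plus a day 1 test in tolvaptan participants where none exists. It needs no extra venepuncture or visit. Some incidental abnormalities will be found in controls and will need follow-up. The second option costs one sentence, but leaves the liver question without a control rate.

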##### Clinical assessment

Daily weight, vital signs and fluid balance (intake and output) will be obtained from the routine electronic medical record. In addition, daily clinical assessment of volume status will be performed to ensure ongoing eligibility and safety.

#### Cognitive/functional assessments

##### Confusion Assessment Method Shortform (CAM-S)

The CAM-S is a widely-used, validated tool for identifying delirium and scoring its severity [34]. It consists of four domains assessing core features of delirium, each assigned a score between 0 and 2 to grade severity. The domains are as follows: acute onset and fluctuating course, inattention, disorganized thinking and altered level of consciousness. The CAM-S is scored by the assessor with a minimum score of 0 and maximum of 7. It will be assessed at baseline (day 1) and repeated 24, 48 and 72 h after commencing the intervention arm (days 2–4) to quantify progress. The CAM has a sensitivity of 94–100%, specificity of 90–95% in detecting delirium and high inter-rater reliability [35, 36].

##### Hyponatraemia symptom questionnaire

A hyponatraemia symptom questionnaire has been devised comprised of two sections. The first is a visual analogue scale scored from 1 to 10 that asks participants to rate their headache, nausea and unsteadiness respectively. Participants will indicate the visual location along a bar from 0 ‘none at all’ to 10 ‘worst you can imagine’. The RedCAP software will calculate a score from 1 to 10 to two decimal places based on the placement of the slider by the participant for each of the three potential symptoms. The second component is the Hyponatraemia Disease-Specific Survey (HDSS), adapted from pre-specified but exploratory symptom evaluation in the SALT-2 tolvaptan trial [13]. There are some similarities to the SF-12 Short Form Health Survey which evaluated wellbeing in both SALT trials; however, that tool is not hyponatraemia-specific [11, 37]. In the HDSS, participants are asked to rate their health over the past day (excellent, very good, good, fair or poor). They are then asked how much their thinking ability has been limited, specifically: Concentrating, Calculating, Language and Memory ability (not at all, slightly, moderately, quite a bit, extremely), which will be scored from 0 to 4 to derive a ‘mental component summary score’ from 0 to 16 (higher score indicating higher level of self-identified limitation). Participants then rate how their strength and coordination has been limited, specifically Endurance, Strength, Gross coordination and Fine coordination (not at all, slightly, moderately, quite a bit or extremely), which are also attributed a number to derive a physical component score 0–16. Additional questions include self-perception of current sodium level without prompting by knowledge of their laboratory test (very low, a little low, normal). Participants are also asked to rate their level of thirst sensation (not thirsty, a little thirsty, normal thirst, extra thirst, very thirsty) and to provide an assessment of their progress ‘Overall, compared to before you came to hospital, how much better do you feel?’ (much better, somewhat better, about the same, somewhat worse or much worse).

##### Timed Up and Go test

The Timed Up and Go test (TUG) is a widely used method to assess function and potentially falls risk that has been endorsed by the American and British Geriatric Societies [38]. Participants are instructed to rise from a standard armchair, walk to a marker 3 m away, turn, walk back and sit down again [39]. It is a marker of physical function, with expected time of completion < 12 s in older adults [40, 41]. It has high test-retest validity [42].

#### Exit questionnaire

An exit questionnaire will be administered by telephone approximately 30 days post discharge. Data will be recorded including length of stay, time to normalization of serum sodium (if achieved beyond the intervention timeframe) and whether re-admission to hospital has occurred. Participants’ wellbeing will be evaluated with the question: ‘Overall, compared to before you came to hospital, how much better do you feel’ (much better, somewhat better, about the same, somewhat worse, much worse). Participant satisfaction with treatment will also be assessed: ‘Overall, how happy were you with your hospital treatment for hyponatraemia (low sodium)?’ (very happy, somewhat happy, neutral somewhat unhappy, very unhappy). The result of serum sodium measurement 30 days post discharge obtained as part of routine care will be collected.

